#### Conservative treatment

Conservative treatment involves a variety of devices by which a patient’s cervical spinal column is rigidly or non-rigidly externally immobilised. Rigid immobilisation is mostly carried out by application of halo-vest traction. Non-rigid immobilisation is achieved by application of a hard cervical collar (e.g. Philadelphia or Miami-J collar). A CRF will register the procedure and motivation for the chosen conservative treatment strategy.

### Baseline assessment

After inclusion and prior to the start of treatment, both surgeon and patient will complete the first set of CRFs. In the case of a surgical treatment, the surgeon will complete a CRF directly after surgery and the patient will complete a second set of CRFs three days after surgery to assess the short-term effect of the operation for the patient. In the case of a conservative treatment, the surgeon will complete a CRF after the application of the immobilisation device.

### Follow-up period

Patients will be seen by the treating surgeon five times for radiological and/or clinical follow-up visits; at 6, 12, 26, 52 and 104 weeks after the start of treatment. In addition to usual patient care, patients will be sent questionnaires (CRFs) to complete at home prior to each follow-up visit (Table 3). On no occasion will patients see the results of earlier assessments. After the last follow-up visit at 104 weeks the patient’s participation in the study ends.

**Table 3 T3:** Data collection and outcome measures

	**Baseline**	**Immediately after start of treatment**	**Weeks of follow-up**				
			**6**	**12**	**26**	**52**	**104**
General status and fracture assessment	**X**						
Demographic data	**X**		**X**	**X**	**X**	**X**	**X**
NDI, MDI, VAS neck pain, SF-36, EQ-5D	**X**	**X***	**X**	**X**	**X**	**X**	**X**
DS14, IPQ-K, Likert			**X**	**X**	**X**	**X**	**X**
Complications of surgery		**X****	**X****	**X****	**X****	**X****	**X****
Secondary surgery			**X****	**X****	**X****	**X****	**X****
Dynamic X-ray					**X**	**X**	**X**
CT-Cervical spine	**X**			**X**	**X****	**X**	

*In case of surgical treatment only.

**When indicated.

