## Background

In the elderly, odontoid fractures are the most common fractures of the cervical spine [1-6]. As the population ages, their incidence and relevance to clinical practice are expected to increase [7]. The treatment for patients with fractures of the odontoid process is based on the fracture pattern, the patient’s medical condition [2] including age, pain, neurological deficits, and the surgeon’s personal preference. Surgical treatment involves anterior odontoid screw fixation or posterior (cranio)atlanto-axial arthrodesis, leading to prompt stability of the upper cervical spine. However, the condition of the patient may deteriorate by undergoing (major) cervical spine surgery [8]. Especially in the very old (≥80 years of age), a surgical intervention has significant risks for the patient. An alternative to avoid the possible complications of cervical spine surgery is conservative treatment with rigid or non-rigid immobilisation for a longer period of time. However, such immobilisation may eventually result in non-union and prolonged fracture instability, requiring secondary surgery [9]. This unnecessarily lengthens treatment duration and, worse, can cause significant deterioration of the cervical spine anatomy and the patient’s condition [10].

Finding the right balance between fracture healing and treatment complications is difficult. In very old patients, finding this balance is even more challenging. In hospitals where upper cervical spine surgery is frequently performed, it is becoming increasingly common to operate on even the very old patient with a cervical spine fracture. However, debate remains as to whether or not this is indeed a favourable development.

Currently available literature reviews on this topic were inconclusive [11,12]. Recent clinical studies focussed on survival and the occurrence of complications, but not on fracture union and stability [13,14]. All other performed clinical studies were carried out retrospectively, were of limited quality and most did not specifically focus on elderly patients. Moreover, minimal attention was paid to grounds for chosen treatments, and patient groups were often poorly comparable. In the vast majority of published studies, only a small number of patients were included (typically <50).

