#### General

•Complications: Complications resulting from the application of the different treatments will be monitored to identify potential differences in the occurrence or severity of complications between treatments.

•Re-interventions/Secondary surgery: One of the goals of the conservative treatment policy is to avoid surgery while still achieving fracture healing and a favourable clinical outcome. The rate of secondary surgery is hence an indication of the success or failure of this policy. Secondary interventions and the cause/motivation for its application will therefore be monitored.

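### Table 3 schedules complications of surgery only, although the protocol plans to compare complications between surgical and conservative treatment; the two need reconciling

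*Protocol article*

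**What the plan says.** All of this is in the protocol article.

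- **Secondary outcome, General.** The outcome covers both strategies: "Complications resulting from the application of the different treatments will be monitored". The stated purpose is to "identify potential differences in the occurrence or severity of complications between treatments".
- **Follow-up period, Table 3.** The only complications row reads "Complications of surgery". It is marked at six time points (immediately after the start of treatment and at weeks 6, 12, 26, 52 and 104), each with the footnote "When indicated". A different footnote, "In case of surgical treatment only", is attached to the immediate post-treatment questionnaires and not to this row.
- **Baseline assessment.** "In the case of a conservative treatment, the surgeon will complete a CRF after the application of the immobilisation device". What that form asks about complications is not stated.
- **Surgical treatment and Conservative treatment.** Each subsection describes a form that records what was done and why. Neither mentions complications.
- **Background.** The clinical problem is framed as a trade-off: "Finding the right balance between fracture healing and treatment complications is difficult".

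**The concern.** The outcome is two-sided, but the only schedule for collecting it is worded for one side. This is a mismatch between two statements that are both printed, so it goes beyond the brevity expected of an article.

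If forms were built from the table label, a surgical patient's wound or implant problem would have a place to be written down, while a conservative patient's pin-site or pressure problem would not. (These are generic examples; the article lists none.) The conservative strategy would then look safer relative to surgery than it is. Later analysis cannot recover events that were never recorded.

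The intention-to-treat rule in the Data analysis section sharpens this. Patients who have surgery after failed conservative treatment stay in their original group. Under a literal reading of Table 3, the only complications with a row in the conservative group would be those of secondary surgery. Complications of immobilisation itself would have none.

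A further, smaller problem affects both groups. When an item is completed only if indicated, an empty field may mean that nothing happened or that nobody asked.

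**Working it through.** The article states no complication rate, no capture rate and no power for this outcome, so there is no figure to reproduce. The check is a comparison of the text, followed by an illustration.

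**Text side by side**

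| Question | Secondary outcome, General | Table 3 | Form descriptions |
|---|---|---|---|
| Which treatments? | Both | Surgery, by its label | Not stated for complications, in either group |
| When? | Not stated | Six time points, when indicated | After surgery or after device application |
| Compared between groups? | Yes | Not applicable | Not applicable |

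Table 3 is therefore the only place that schedules the collection of complications, and its label is narrower than the outcome it serves. The visits are not the obstacle: all patients have the same five surgeon visits, at 6, 12, 26, 52 and 104 weeks.

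**What a literal reading would do**

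Let *p* be the true complication rate, taken as equal in both groups. Let *t* be the fraction of events captured in the surgical group and *s* the fraction captured in the conservative group.

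- Observed rates: *pt* (surgical) and *ps* (conservative).
- Spurious difference, surgical minus conservative: *pt* − *ps* = *p*(*t* − *s*).
- With full capture after surgery (*t* = 1), this becomes *p*(1 − *s*).

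The values of *p* and *s* below are assumptions; the article gives neither. Entries are percentage points by which surgery would look worse, with *t* = 1.

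| True rate *p* | *s* = 1 | *s* = 0.75 | *s* = 0.5 | *s* = 0 |
|---|---|---|---|---|
| 20% | 0 | 5 | 10 | 20 |
| 30% | 0 | 7.5 | 15 | 30 |
| 40% | 0 | 10 | 20 | 40 |

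For example, 20% × (1 − 0.5) = 10 points.

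Two features matter more than any single cell:

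- **The direction is fixed by the label.** If capture differs because the row names surgery, then *s* < *t* and the bias runs against surgery.
- **Unequal capture is what matters, not incomplete capture.** If *t* = *s*, this spurious difference is zero, even when both are below 1.

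**The case against.** The strongest reply is that this is a loosely worded row label and no more.

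- The outcome text says plainly that complications of both treatments will be monitored.
- Table 3 has a footnote for items confined to surgical patients, and the complications row does not carry it.
- A surgeon completes a form after treatment starts in both groups, and the follow-up visits are identical.
- The two form descriptions are close to parallel, and neither mentions complications, so they show no asymmetry.
- The article condenses a fuller protocol. Complication lists, grading and definitions may well be there, and their absence here is no fault.
- Complications are a secondary outcome. Other harm-related information is not tied to one treatment: secondary surgery has its own row, and causes of death will be examined against the treatment applied.

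Most of this stands. A reader might infer from Table 3 that conservative harms are in fact under-recorded and that the comparison is already biased. The documents do not support that. It would follow only if the forms apply the label literally, and the forms are not shown. Zero capture in the conservative group would also go against the stated outcome, so the right-hand column of the illustration is a bound and not an expectation. The footnote for indicated items does not itself separate the groups, since it covers the whole row.

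The reply does not remove the mismatch. A missing surgical-only footnote does not widen a row whose own label says surgery, and no other text in the article schedules the collection of immobilisation complications.

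**Conclusion.** The point holds as an internal inconsistency with a conditional consequence. Table 3 schedules complications of surgery, while the outcome requires complications of either treatment. If the case record forms follow the table, complications of halo or collar immobilisation would be under-ascertained, and the comparison of occurrence and severity would be biased against surgery.

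The size cannot be derived from the document. The tabulated values of 0 to 40 points depend entirely on the assumed rate and capture fractions, on equal true rates and on full capture after surgery.

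The consequence is confined to one secondary outcome. Union, stability and NDI improvement at 52 weeks are unaffected, as is the target of 275 patients. Correction is still worthwhile, because the Background treats complications as one side of the treatment balance and because lost events cannot be restored at analysis.

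**What to change.** Reconcile Table 3 with the complications outcome:

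1. Relabel the row as complications of treatment, surgical or conservative.
2. Record it for every patient in both groups at the same visits, using the same definitions.
3. Include an explicit entry for none, so that an empty field is not read as the absence of a complication.

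The cost is one form item at visits that already take place, plus a correction to the table. If the forms already collect this for both groups in the same way, only the label needs changing. The change concerns data collection only; it alters no treatment, no primary analysis and no sample size.

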### Primary outcome

The primary outcomes are fracture healing and clinical outcome at 52 weeks after the start of treatment:

•Fracture healing will be scored by assessing union (union or non-union) and stability (stable or unstable).

o Union will be defined by evidence of bone trabeculae crossing the fracture site and absence of sclerotic borders adjacent to the fracture site, assessed using computed tomography (CT).

o Fracture stability will be assessed using upright cervical dynamic X-rays in lateral projection. A maximum of 2 mm movement at the fracture site is considered stable, over 2 mm movement at the fracture site is considered unstable [15].

•Clinical outcome; scored by calculation of the improvement compared to baseline in the Neck Disability Index (NDI) [16] score at 52 weeks after start of treatment. The NDI is a widely applied instrument to assess neck pain complaints. It was derived from the Oswestry index for back pain and the Pain Disability Index.

In the sample size calculation, the significance level was adjusted for the multiple primary outcome measures.

### Secondary outcome

Secondary clinical outcome parameters will be assessed by questionnaires to be completed by the patient. At baseline they will be completed at the hospital. During the follow-up period, they will be sent to the patient’s home. Radiological outcome parameters will be assessed by questionnaires to be completed by the treating surgeon and, in addition, again at the coordinating centre.

#### Clinical

•Myelopathy Disability Index (MDI) [17]: The MDI is a functional scoring system for cervical myelopathy that was originally designed for patients with rheumatoid arthritis. It consists of a selection of questions from the Standford Health Assessment Questionnaire.

•Visual Analogue Scale (VAS) for neck pain [18,19]: The VAS neck pain score indicates the intensity of experienced neck pain by drawing a mark on a 100 mm line. 0 mm symbolises ‘no pain’ , 100 mm symbolises ‘pain as worse as it could possibly be’.

•Short Form-36 (SF-36) [20,21]: The SF-36 is a generic health survey consisting of 36 questions. It consists of eight domains: physical functioning, physical restrictions, emotional restrictions, social functioning, somatic pain, general mental health, vitality and general health perception. It results in physical and mental health summary measures and a health utility index.

•EuroQol 5 Dimensions (EQ-5D) [22]: The EQ-5D is a tool to measure health outcome. It yields a descriptive profile and single index value for the patient’s health status.

•Type D Scale 14 (DS14) [23]: The DS14 is a standard assessment of negative affectivity, social inhibition, and Type D personality.

•Illness Perception Questionnaire-K (IPQ-K) [24]: The IPQ-K is a brief illness perception questionnaire, using a nine-item scale to rapidly assess the cognitive and emotional representations of the patient’s illness.

•Likert scale on recovery: The Likert scale used for this study is a seven-point scale on the patient’s perceived recovery from complaints and neck pain.

Not all of these questionnaires were already validated in the native languages of all countries involved in this trial. Therefore, prior to the start of the study they were validated by a process of bilateral translation. A native speaker of the target language who was also fluent in English first translated the questionnaire into the target language. A native speaker of English who also spoke the target language and was blinded to the original text then translated the text back into English. The original text and the back translated text were then compared at a consensus meeting. If the meaning of the two texts was agreed to be identical, the question was assumed to be adequately translated. Possible differences were discussed. More extensive options for transcultural adaptation of questionnaires were not considered feasible or necessary in the context of this trial.

#### Radiological

•Fracture displacement and direction: Displacement will be assessed by drawing lines along the posterior and lateral aspects of the odontoid process and the caudal body of C2. Displacement is expressed in mm. Direction is categorised as anterior, posterior, lateral, anterior-lateral or posterior-lateral.

•Grade of osteoporosis in C2: Osteoporosis will be classified according to the following criteria [4,25];

o None: normal trabecular pattern with normal cortical thickness.

o Mild: decrease in the amount of trabeculae with no areas of holes and normal cortical thickness.

o Moderate: absent trabeculae (holes) involving less than 25% of the transverse diameter of the bone with cortical thinning.

o Severe: absent trabeculae (holes) involving more than 50% of the transverse diameter of the bone with cortical thinning.

•Grade of degeneration in C0-C2 joint: Facet joint degeneration will be classified according to the following criteria [4,25];

o None: normal joint space with no osteophyte formation.

o Mild: narrowed joint space or normal joint space with osteophyte formation.

o Moderate: obliterated joint space with or without osteophyte formation.

o Severe: completely obliterated joint space, ankylosis or fusion of the joint.

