## Abstract

**Background:**

Fractures of the odontoid process of the axis are the most common fractures of the geriatric cervical spine. As the population ages, their incidence is expected to increase progressively, as is the number of very old patients (>80 years) with an odontoid fracture. No consensus exists on the optimal treatment (surgical or conservative) and the most relevant outcome parameter (osseous union, fracture stability or clinical outcome). The aim of the INNOVATE (INterNational study on Odontoid frActure Treatment in the Elderly) Trial is to prospectively assess fracture healing and clinical outcome after surgical and conservative treatment for odontoid fractures in the elderly patient, with a specific focus on the very old patient.

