**Methods/Design:**

The trial is an observational study in which eleven centres in five European countries are involved. All patients admitted to one of these centres who meet the selection criteria (≥55 years, acute (<two weeks) type II/III odontoid fracture, no rheumatoid arthritis, no ankylosing spondylitis, no previous treatment for odontoid fracture) are asked to participate. The applied treatment is in accordance with usual care and chosen by the treating surgeon and patient. A cohort of 275 patients will be included. Clinical and radiological follow-up moments are scheduled at 6, 12, 26, 52 and 104 weeks, at which both surgeon and patient will complete Case Record Forms (CRFs). The primary outcome will be a combination of fracture healing and clinical outcome at 52 weeks. Osseous union and fracture stability will be assessed with CT-imaging and dynamic X-ray. Clinical outcome will be scored by the Neck Disability Index (NDI) and correlated to the imaging data. Additionally, predefined subgroup analysis will be carried out (i.e. for patient age and osteoporosis) and prognostic factors will be identified.

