Furthermore, the goal of treatment is still debatable. It is unknown whether or not non-union always leads to complaints in the patient. Consequently, debate remains as to whether the goal of treatment should be osseous union, fracture stability or a favourable clinical outcome. The measurement of these parameters is likewise not uniformly described. The available literature shows higher osseous union rates in surgically compared to conservatively treated patients (66–85% and 28–44%, respectively), but patient selection mechanisms may have profoundly interfered with these outcome percentages. The majority of patients achieved fracture stability regardless of the applied treatment (82-97% in surgically treated patients and 53-79% in conservatively treated patients). There are insufficient data available, especially from direct comparisons, to determine the difference in clinical outcome between surgical and conservative treatment strategies. There is no evidence that clinical outcome correlates better to fracture union than to fracture stability, or that the quality of union, whether it be osseous of fibrous, influences clinical outcome [12].

The goal of this study is to prospectively compare fracture union, fracture stability and NDI improvement at 52 weeks between surgical and conservative treatments in patients over 55 years of age with acute type II and III odontoid fractures. Predefined subgroup analysis may offer prognostic factors that can predict the success of either a surgical or conservative treatment. The influence of age (≥55-80 and ≥80 years) on treatment outcome will particularly be studied. The outcome of this study will yield valuable information enabling more rational decision making in treating the elderly patient population.

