#### Multivariate analysis

Multivariate analyses will be carried out using regression models with dichotomised union, stability and NDI as dependent variables, and with the secondary outcome parameters as independent variables and covariates. Propensity score analysis will be used to generate a model to predict the treatment received with the baseline variables:

•Patient age (both dichotomised (≤80 and >80 years) and continuous)

•Fracture characteristics (type of fracture)

•Fracture displacement (in mm and direction)

•Severity of osteoporosis in C2

•Facet joint degeneration in C1-C2

•NDI

•MDI

•VAS neck pain

•SF-36

•EQ-5D

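### The C2 osteoporosis scale gives no grade to holes covering 25–50% of the bone diameter, and the age cut at 80 and the facet joint level differ between sections

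*Protocol article*

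**What the plan says.** **Osteoporosis.** Under Secondary outcome, Radiological, the article grades C2 osteoporosis in four steps, citing published criteria. The lowest grade requires a normal trabecular pattern and normal cortex. The other three are:

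- "Mild: decrease in the amount of trabeculae with no areas of holes and normal cortical thickness"
- "Moderate: absent trabeculae (holes) involving less than 25% of the transverse diameter of the bone with cortical thinning"
- "Severe: absent trabeculae (holes) involving more than 50% of the transverse diameter of the bone with cortical thinning"

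The abstract (Methods/Design) states that "predefined subgroup analysis will be carried out (i.e. for patient age and osteoporosis"). Severity of osteoporosis in C2 is also in the baseline list for the propensity score under Multivariate analysis.

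**Age.** The last paragraph of the Background says: "The influence of age (≥55-80 and ≥80 years) on treatment outcome will particularly be studied". The propensity list under Multivariate analysis has: "Patient age (both dichotomised (≤80 and >80 years) and continuous"). The abstract's background refers to "the number of very old patients (>80 years) with an odontoid fracture". The first paragraph of the main Background writes: "Especially in the very old (≥80 years of age), a surgical intervention has significant risks for the patient". The Discussion speaks of patients younger than 80 and older than 80.

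**Facet joints.** The Radiological section grades degeneration of the C0-C2 joint. The propensity list names C1-C2.

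**The concern.** A grading scale used in an analysis should place every patient in exactly one category. Here the top of one grade (below 25%) and the bottom of the next (above 50%) do not meet, and no other grade can take the patients in between. The Radiological section presents these criteria as the ones by which patients will be classified, so this is the working definition.

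The grade is used in several analyses. It defines one of the two named subgroups, it is a propensity covariate, and as a listed secondary outcome it is a candidate independent variable in the regression models. Surgeon and patient choose the treatment together, and the propensity score is the method the article names for modelling that choice. According to the Secondary outcome section, radiological parameters are scored by the treating surgeon and again at the coordinating centre. With eleven centres and no rule for the middle band, readers can settle the same image differently.

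Age is the other named subgroup factor, and very old patients are the study's declared focus. If the cut differs between the aim and the analysis list, two analysts following the article could form different strata. The joint level raises a similar question: is the variable that is graded the same one that is modelled?

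**Working it through.** The plan gives no figure to reproduce. The check is whether each possible value falls in exactly one category.

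**Step 1: osteoporosis, with cortical thinning present.** Inputs are the four grade definitions in the Radiological section.

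| Holes, % of transverse diameter | Grade under the printed criteria |
|---|---|
| 10 | Moderate |
| 24.9 | Moderate |
| 25 | none fits |
| 30 | none fits |
| 40 | none fits |
| 50 | none fits |
| 50.1 | Severe |
| 75 | Severe |

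The ungraded range is the closed interval from 25% to 50%, both endpoints included. The two lower grades cannot absorb it, because one requires a normal trabecular pattern, the other requires the absence of holes, and both require normal cortex.

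The same strict reading shows a smaller gap. Holes without cortical thinning, or thinning without holes, also match no grade, because each definition joins a trabecular and a cortical condition.

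**Step 2: age.** Inputs are the five places that mention 80.

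| Place | Age 79 | Age 80 | Age 81 |
|---|---|---|---|
| Abstract, background (>80) | not very old | not very old | very old |
| Background, first paragraph (≥80) | not very old | very old | very old |
| Background, study goal (≥55-80 and ≥80) | younger | both, as printed | older |
| Multivariate analysis (≤80 and >80) | younger | younger | older |
| Discussion (younger and older than 80) | younger | neither, if literal | older |

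Only age 80 is affected. If the study goal's 55-80 means up to the 80th birthday, the overlap in that sentence disappears. Age 80 is then in the older group in the study goal and still in the younger group under Multivariate analysis.

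How much this matters depends on how age is stored, which the article does not say. In completed years, everyone between the 80th and 81st birthdays changes group with the rule chosen. With exact age, a patient aged 80.4 is in the older group under both ≥80 and >80, and only a patient exactly on the 80th birthday moves.

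**Step 3: facet joints.** The graded site is C0-C2 and the modelled site is C1-C2. The labels differ, and the article does not say how one value is obtained from the other.

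**Step 4: reach.** The primary analysis under Univariate analysis consists of χ² tests for union and stability and a t-test for NDI improvement, between treatment groups. None uses osteoporosis, the age cut or facet grade. The sample size calculation does not use them either.

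**The case against.** The strongest reply has four parts.

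- **Age is partitioned where it is analysed.** The list under Multivariate analysis (≤80 and >80) places every patient once, agrees with the abstract's background and adds continuous age, which no cut can disturb. The conflicting wording is in the Background. This stands in part: it would be wrong to say that the age categories fail everywhere, or that the cut is simply open to choice after the data are seen. But that list belongs to the propensity model, while the ≥80 wording belongs to the subgroup aim, so the subgroup cut is still ambiguous.
- **The gap may come from the cited classification, or reading forms may settle it.** Neither source can be checked here. If the published scale has the same gap, redefining a grade would depart from it, which is why the source should be checked first. This possibility does not repair the criteria as printed.
- **C1-C2 lies within C0-C2**, so the joint mismatch may be loose labelling. That is plausible, and one word would settle it.
- **The effect is limited**, because the primary tests use none of these variables. This stands.

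A reader might also infer that 25–50% of patients go ungraded, or that a definite number of patients is lost. The percentages refer to bone diameter, and the article gives no distribution of grades and no age distribution around 80. Nor does it support the inference that these patients would drop out selectively through a complete-case analysis: it states no such handling, and missing-data rules may be in an analysis plan that is not shown.

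**Conclusion.** The point holds as a defect of definition. As printed, the osteoporosis scale leaves holes covering 25% to 50% of the transverse diameter without a grade, in a variable that is both a named subgroup factor and a propensity covariate. Such patients would be ungraded or graded ad hoc. How many there would be cannot be known from the document.

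The age cut is inconsistent at age 80 only. It has practical weight if age is recorded in completed years and almost none if exact age is used. The facet joint level differs between its definition and its use in the model.

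The consequences are confined to the subgroup, regression and propensity analyses. The three primary tests and the target of 275 patients are unaffected. The conclusion rests on reading the printed criteria as the operative ones.

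**What to change.** 1. Check the cited classification, then reword the osteoporosis grades so that every combination of hole extent and cortical thickness falls in exactly one grade. Re-code any images already read that lie in the gap.
2. State one age cut-off and use it throughout, for both the subgroup analysis and the propensity model, fixed before analysis. Say whether age is held in completed years.
3. Name the same joint level for facet degeneration in the Radiological section and in the propensity list.

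The cost is a few lines of definition, a short instruction to readers and re-coding of any affected images. No new data are needed, and neither the sample size nor the primary analysis changes.
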